## 7.4 Exclusion Criteria

Patients must be excluded from participating in this study if they meet any of the following criteria:

- The patient has another confirmed condition that can fully account for the cognitive impairment, including but not limited to psychiatric disorders (schizophrenia, mood disorders, bipolar disorder and personality disorders); neuroinflammatory, neuroinfective, or neurodegenerative diseases; multiple sclerosis; genetic disorders; HIV; brain injuries; neurosurgery aftereffects, delirium). Patients with long-known, stabilized psychiatric or other brain conditions that cannot fully account for the cognitive impairment may be included in the study.
- The patient comes to observation for reasons other than diagnosis (disability assessment for social aids, cognitive assessment for driving license, etc.)
- The patient had a previous A $\beta$  imaging scan and/or has had other AD biomarker workup (fluorodeoxyglucose [FDG]-PET and/or cerebrospinal fluid [CSF] analysis) prior to screening. In some centres, the patient may receive a diagnostic workup before screening. These patients can be enrolled if the investigator is blind to the results until after randomization.
- The patient has a life-threatening unstable medical disease or psychiatric condition that could lead to difficulty in complying with the protocol.
- The patient is currently receiving an investigational pharmaceutical product or has participated in a clinical trial with an investigational pharmaceutical product within 30 days prior to screening, and/or was administered a radiopharmaceutical within 10 radioactive half-lives prior to study drug administration in this study.
- The patient is a woman who is pregnant, planning to become pregnant, or lactating. Pregnancy status of a woman with childbearing potential will be carried out before the PET scan. A woman is considered of childbearing potential (WOCBP), i.e. fertile, following menarche and until becoming post-menopausal unless permanently sterile ([www.hma.eu/ctfg.html](http://www.hma.eu/ctfg.html), Recommendations related to contraception and pregnancy testing in clinical trials, September 2014).
- The patient is not affiliated to the Social security and does not receive the rights and corresponding coverage, in accordance with the Code of Public Health.

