##### 10.1.2.3 Health economics

- The impact on patient-related outcomes (cognition, anxiety, depression, coping skills, and quality of life) at T3 vs T2 vs T0 in each arm

- The difference in the cost of diagnostic workup to the etiologic diagnosis with very high confidence ( $\geq 90\%$ ) in the Early Amyloid PET Imaging arm vs the Late Amyloid PET Imaging arm. (In those centres where the subjects in the Early Amyloid PET Imaging arm receive a diagnostic workup in addition to clinical evaluation before baseline, the relative costs will not be considered if the results of those exams are not known by the managing physician before the managing physician makes the etiologic diagnosis.)
- Differences in the use of medical resources (not limited to diagnostic procedures, tests, visits, and hospitalisations) and programs between Early Amyloid PET and Late Amyloid PET arms.
- The number of patients who withdraw from the study and the reasons for withdrawal.

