### **10.3.14 Patient questionnaire (use of medical resources)**

Data from the patient questionnaire on the use of medical resources will be collected at T0, T1, T2, and T3 and recorded in the eCRF. (T1 does not require a clinic visit.)

In those centres where the participants in the Early Amyloid PET arm receive a diagnostic workup in addition to clinical evaluation before baseline, the relative costs will not be considered if the results of those exams are not known by the managing physician before the managing physician makes the etiologic diagnosis.

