### **12.5.3 Handling of missing values/censoring/discontinuations**

The reasons for incomplete data are many and include major protocol deviations, dropout because of study withdrawal or death, non-attendance at clinical visits, missing questionnaire items, uninterpretable images, etc.

The primary efficacy analysis will be conducted on the PPS population, which is based on complete cases.

Secondary efficacy analyses will be conducted on the FAS population. In time-to-event analyses, dropout and major protocol deviations are accounted for by censoring at the time of dropout or protocol deviation. In cross-sectional analyses and analyses of change between 2 timepoints, only complete cases will be included. Cases with a major protocol deviation before the first timepoint in the cross-sectional or change analysis will be excluded. The longitudinal mixed-effect analyses will be based on the observed cases. Data will be censored after a major protocol deviation. The underlying assumption in all analyses is that missing data are missing at random and not related to the primary outcome.

The proportion of missing data at each time point will be computed for the Early Amyloid PET, Late Amyloid PET, and Free Choice arms separately, and stratified for SCD Plus, MCI, and dementia.

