#### **12.6.1.3 Health Economics Objectives**

- The impact on patient-reported outcomes (cognition, anxiety, depression, coping skills, and quality of life) at T3 vs T2 vs T0 in each arm
- The difference in the cost of diagnostic workup to the etiologic diagnosis with very high confidence ( $\geq 90\%$ ) in the Early Amyloid PET arm vs the Late Amyloid PET arm. (In those centres where the participants in the Early Amyloid PET arm receive a diagnostic workup in addition to clinical evaluation before baseline, the relative costs will not be considered if the results of those exams are not known by the managing physician before the managing physician makes the etiologic diagnosis.)
- The difference between arms (Early Amyloid PET vs Late Amyloid PET vs Free Choice) in the use of medical resources (not limited to diagnostic procedures, tests, visits, and hospitalisations) and programs.

- The number of patients who withdrew from the study, and the reasons for withdrawal.

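### The rule that drops unseen pre-baseline work-up costs names only the Early PET arm, so it can only move the Early-versus-Late cost difference towards Early PET, by an unknown and possibly small amount

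*Protocol*

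**What the plan says.** The endpoint in Protocol Section 10.1.2.3 is "The difference in the cost of diagnostic workup to the etiologic diagnosis with very high confidence" (at least 90%), Early arm versus Late arm. A parenthesis adds a costing rule: where, at some centres, those randomised to "the Early Amyloid PET Imaging arm receive a diagnostic workup in addition to clinical evaluation before baseline, the relative costs will not be considered". The rule carries a condition: costs are dropped only "if the results of those exams are not known by the managing physician before the managing physician makes the etiologic diagnosis".

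The rule appears twice more. Section 10.3.14 opens it with "In those centres where the participants in the Early Amyloid PET arm receive a diagnostic workup in addition to clinical evaluation before baseline", and Section 12.6.1.3 says that "the relative costs will not be considered if the results of those exams are not known by the managing physician" before the diagnosis is made. All three places name the Early arm and no other. The synopsis version of the endpoint carries no costing rule.

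Four other provisions bear on how the rule works:

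- Section 7.4 excludes patients with earlier AD biomarker work-up but makes an exception: "In some centres, the patient may receive a diagnostic workup before screening". It continues: "These patients can be enrolled if the investigator is blind to the results until after randomization". The exception does not depend on arm.
- Section 8.3.2 randomises 1:1:1, stratified by centre and syndromic diagnosis.
- Section 13.2 keeps the managing physician of an Early-arm participant blind to other test results until the amyloid PET result is available.
- Section 9.2 has test results that are available at baseline reviewed and recorded then in the Late and Free Choice arms.

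**The concern.** Work-up done before baseline is paid for before anyone knows the arm, so randomisation makes its mean cost equal across arms in expectation. A rule that removes part of this cost from one arm, and says nothing about the other, changes the comparison without any difference in resource use.

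The protocol also makes the triggering condition more likely in the arm that benefits. Section 13.2 keeps results unseen in the Early arm for a time, while Section 9.2 opens available results at baseline in the Late arm. A Late-arm participant whose physician reached the diagnosis without the pre-baseline results would still be charged for them.

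Section 4.1.3 lists costs and cost-effectiveness of early versus late adoption among the things the study will determine, and Section 4.1.1 says the study will supply input for economic modelling. A costing rule that can favour only one arm would carry into both.

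**Working it through.** The protocol states no unit cost, no expected cost difference and no power for the cost endpoint, so there is no figure of the plan's own to reproduce. The check is expected-value algebra.

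**Inputs (none given in the protocol, all assumed)**

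- p: share of participants with pre-baseline work-up, equal in both arms in expectation because of randomisation (Section 8.3.2).
- c: mean cost of that work-up, taken as the same whether or not the results were seen.
- qE, qL: among those with work-up, the share whose results were unknown to the managing physician at the diagnosis, in Early and Late.

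**Mean pre-baseline cost counted per participant**

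| Costing rule | Early | Late | Early − Late |
|---|---|---|---|
| As written | p·c·(1 − qE) | p·c | −p·c·qE |
| (A) All tests counted in both arms | p·c | p·c | 0 |
| (B) Same conditional rule in both arms | p·c·(1 − qE) | p·c·(1 − qL) | −p·c·(qE − qL) |

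**Shift caused by the one-arm wording**

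- Against (A): −p·c·qE − 0 = −p·c·qE.
- Against (B): −p·c·qE + p·c·(qE − qL) = −p·c·qL.

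Both are zero or negative for any admissible inputs. The sign does not depend on the assumed values: against (A) a non-negative cost is removed from Early only, and against (B) a non-negative cost is left in Late only.

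**Range, in multiples of c, for assumed inputs**

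| Comparison | Inputs | Shift |
|---|---|---|
| Against (A) | p = 0.10, qE = 0.2 | −0.10 × 0.2 = −0.02c |
| Against (A) | p = 0.25, qE = 0.5 | −0.25 × 0.5 = −0.125c |
| Against (A) | p = 0.50, qE = 0.8 | −0.50 × 0.8 = −0.40c |
| Against (B) | any p, qL = 0 | 0 |
| Against (B) | p = 0.25, qL = 0.1 | −0.25 × 0.1 = −0.025c |
| Against (B) | p = 0.50, qL = 0.2 | −0.50 × 0.2 = −0.10c |

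**Can qL be above zero?** Section 9.2 opens available results at baseline in the Late arm, which pushes qL down. The same section asks for several hypotheses only where confidence above 90% has not been reached for a single one. A high-confidence diagnosis at baseline is therefore possible in any arm, and it may precede the opening of those results. So qL may be small but need not be zero.

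**The case against.** The strongest reply is that the rule has a sensible purpose. The endpoint is the cost of work-up leading to the diagnosis, and the Early arm is a PET-first strategy: PET takes priority over other exams except MRI (Section 6.1.1), and other results are withheld until it is read. A test that nobody saw before the diagnosis did not help to reach it. Costing tests used rather than tests performed is a legitimate target. Under that target most of the Early-minus-Late difference belongs to the comparison, and the fault is only −p·c·qL. This stands, and it limits the size. It does not justify naming one arm, because the same logic applies to an unseen test in the Late arm.

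A reader might infer that all pre-baseline cost is removed from the Early arm. The text does not say so. Blinding in that arm ends when the PET result is available, and Section 6.1.1 requires each biomarker result up to Week 12 to reach the physician. Tests opened before the diagnosis still count.

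A reader might also infer a definite false saving in money. That would treat (A) as the only correct rule and would need values for p, c and qE. The protocol gives none, and Section 7.4 admits prior biomarker work-up only as an exception at some centres.

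Finally, a reader might infer that participants who never reach 90% confidence fall out of the cost analysis, because Section 12.5.3 says of cross-sectional and change analyses that "only complete cases will be included". That section does not say that such participants count as missing for cost, and their handling is commonly left to the statistical analysis plan, which is not shown. This is not part of the point.

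**Conclusion.** The point holds as a one-sided rule of known direction and unknown size. Followed as written, it can only move the Early-minus-Late cost difference in favour of Early PET: by −p·c·qE against counting every test in both arms, and by −p·c·qL against the same conditional rule in both arms. For the assumed inputs tried, these run from −0.02c to −0.40c and from 0 to −0.10c. The second comparison is the fairer measure if the sponsor's target is tests that informed the diagnosis, and there the effect may be close to nothing.

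The direction rests only on the wording of the three sections. The size rests wholly on inputs that the protocol does not supply. One of many secondary endpoints is affected; the primary endpoint is not.

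**What to change.** In Sections 10.1.2.3, 10.3.14 and 12.6.1.3, replace the reference to the Early arm with one rule for all compared arms: exclude, in every arm, the cost of any pre-baseline test whose result the managing physician did not know before making the etiologic diagnosis. Add a sensitivity analysis that counts all pre-baseline tests in every arm, so that readers can see how far the result depends on the choice.

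The cost is a change of one sentence in each of three places and one small extra analysis. The apparent saving for Early PET may become smaller. If unseen results prove rare in the Late arm, the common rule will change almost nothing, and the report can then say so.

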#### **10.1.2.4 Quantitative imaging results assessment**

In addition to the local visual read of the PET image used for the primary and secondary (diagnosis and confidence) endpoints, PET images will be analysed centrally by the Sponsor for quantitative imaging endpoints, as follows.

For all subjects (initial amyloid PET scan only):

- The distributions and mean standardised uptake value ratio (SUVR) of the composite cortical brain regions, and converted to the centiloid scale, across amyloid PET tracers and by diagnostic subgroup.
- The distributions and mean SUVR of defined brain regions across amyloid PET tracers and by diagnostic subgroup.
- For each of the amyloid PET tracers, the composite cortical quantitative uptake (SUVR and SUVR converted to the centiloid scale) versus the local site visual reading interpretation and classification confidence.

For subjects in the Early Amyloid PET Imaging arm who have a second amyloid PET scan:

- The distributions and mean change in standardised uptake value ratio (SUVR) of the composite cortical brain regions, and converted to the centiloid scale, across amyloid PET tracers and by diagnostic subgroup.
- The distributions and mean change in SUVR of defined brain regions across amyloid PET tracers and by diagnostic subgroup.

#### **10.1.3 Image acquisition**

The instructions for acquiring the amyloid PET images are provided in the Imaging Manual.

NeuraCeq, Vizamyl and flutemetamol ( $^{18}\text{F}$ ) images should be acquired starting at 90 minutes after intravenous injection. The scan duration should typically be 20 minutes.

#### **10.1.4 Image storage**

The contract research organization IXICO will be hosting image storage (NeuraCeq, Vizamyl and flutemetamol [ $^{18}\text{F}$ ] images) on their Trial Tracker platform for this study.

### 10.1.5 Image interpretation

The local site interpretation of the amyloid PET images will be performed by readers who have undergone the tracer-specific reader training provided by Piramal (for NeuraCeq™) and GEHC (for Vizamyl™) and training in the eCRF completion.

For information about image interpretation, see the accompanying Imaging manual.

### 10.1.6 PET data reporting

Electronic case report forms that are specific to the reading methodology for the given tracer will be used by the investigator to record the results of the amyloid PET scan, classification as positive or negative and a rating of classification certainty.

## 10.2 Safety Assessments

The investigator(s) and the Sponsor will review the safety data. The following will be recorded:

- Conditions that started before the informed consent form was signed will be recorded as medical/surgical history.
- Adverse events (AEs) that occur within 48 hours of study drug administration will be recorded.
- SAEs occurring within 30 days of study drug administration will be recorded.

### 10.2.1 Treatment-emergent adverse events

**AE Definition:** An AE is defined as any untoward medical occurrence in a patient or clinical investigation participant administered a pharmaceutical product and which does not necessarily have to have a causal relationship with this treatment. An AE can therefore be any unfavourable and unintended sign (including an abnormal laboratory finding), symptom, or disease temporally associated with the use of an IMP, whether or not considered related to that product. Only symptoms/signs that begin or worsen in severity and/or frequency after IMP administration/use will be recorded as AEs in the eCRF.

The participants will be closely observed and questioned for any kind of AE during the study procedures and at follow-up appointments throughout the study period with non-leading questioning (e.g., “How do you feel?”). The participants will be instructed to immediately report any symptoms and signs to the study staff (i.e., between formal observations).

All AEs that occur within 48 hours of study drug administration will be recorded.

Both the investigator(s) and Sponsor will perform a causality assessment on any AE, to assess whether or not there is a reasonable possibility (evidence to suggest) that the IMP caused the event.

**Adverse Reaction:** An AE that is caused by the IMP.

**Suspected Adverse Reaction:** A reasonable possibility exists for causality between the IMP and the AE

#### 10.2.1.1 Expected adverse events

The reference safety information for the determination of adverse drug reactions will be the SmPC for florbetaben ( $^{18}\text{F}$ ) [NeuraCeq™ SmPC], the SmPC for VizamyI™ [VizamyI SmPC], and the Investigator Brochure for Flutemetamol ( $^{18}\text{F}$ ) Injection [ $^{18}\text{F}$  Flutemetamol].

#### 10.2.1.2 Expected conduct-related AEs

The use of an indwelling venous cannula for the administration of study drug may be accompanied by mild bruising and also, in rare cases, by transient inflammation of the vessel wall. After initial irritation, the presence of an indwelling cannula is usually painless and hardly noticeable. The same applies to single vein punctures for blood sampling.

#### 10.2.1.3 Expected adverse drug reactions

Please see the SmPC for the possible side effects of NeuraCeq™ [NeuraCeq™ SmPC] and VizamyI™ [VizamyI SmPC] and the Investigator Brochure for Flutemetamol ( $^{18}\text{F}$ ) Injection [ $^{18}\text{F}$  Flutemetamol].

These radiopharmaceuticals will deliver low amounts of ionizing radiation associated with the least risk of cancer and hereditary abnormalities.

However, AEs from the radioactive dose are not expected, since the applied radiation doses are far below doses that can cause acute effects in human tissues.

#### 10.2.1.4 Precautionary measures

Special precautionary measures are not considered to be necessary for this study. In case of emergency, standard emergency procedures will be employed.

#### 10.2.1.5 Unexpected adverse drug reactions

An unexpected adverse drug reaction is defined as an adverse reaction in the nature and severity which is not consistent with the applicable product information (e.g., in the SmPC or in the IB). Any adverse experience that is not listed in the current SmPC or IB with regard to the specificity or severity shall be regarded as unexpected. “Unexpected” as used in this definition refers to an adverse drug experience that has not been previously observed and included in the product information, rather than from the perspective of such experience not being anticipated from the pharmacological properties of the investigational product.

#### 10.2.2 Serious adverse events

An SAE is defined as any AE that:

- Results in death.
- Is life threatening.
- Requires in-patient hospitalisation or prolongation of existing hospitalisation.

- Results in persistent or significant disability or incapacity.
- Is a congenital anomaly or birth defect.
- Is another important medical event.\*

(\*Other important medical events are those that may not result in death, be life threatening, or require hospitalisation, but may be considered an SAE when, based upon appropriate medical judgment, they may jeopardise the participant and may require medical intervention to prevent one of the outcomes listed above.

All SAEs occurring within 30 days of study drug administration will be recorded.

### **10.2.3 Adverse event and serious adverse event reporting**

All AEs should be recorded using acceptable diagnoses, if possible. If an AE has already been reported it is not necessary to report each individual sign and symptom of that AE as a separate AE. For example, if myocardial infarction is reported as an AE, there is no need to report elevated creatine kinase and abnormal ECG, or other related signs, symptoms, or laboratory values as separate AEs. However, if both occurred in isolation and myocardial infarction was not diagnosed, then each event would be reported as an AE.

The intensity of all AEs will be graded as mild, moderate, or severe using the following definitions:

|           |                                                                      |
|-----------|----------------------------------------------------------------------|
| Mild:     | Tolerable.                                                           |
| Moderate: | Interferes with normal activity.                                     |
| Severe:   | Incapacitating (causes inability to perform usual activity or work). |

The investigator will be instructed to closely monitor each participant who experiences an AE (whether ascribed to the IMP or not) until the outcome of the AE has been determined.

In addition to the investigator's own description of the AEs, each AE will be encoded by the Sponsor/CRO according to a well-recognised dictionary of medical codes.

SAEs will be recorded in the eCRF if they occurred as follows:

- After a participant first received an IMP and throughout the participant's follow-up period\*, whether or not considered related to the IMP, and
- After the participant's follow-up period, and for which a causal relationship to the IMP cannot be ruled out.

(\*Follow-up period is defined as the protocol-stipulated period or, for participants prematurely withdrawn from a study, the duration of a participant's participation.)

All serious and non-serious AEs must be followed for a final outcome until the end of the follow-up period. An outcome of "unknown" is not considered to be an acceptable final outcome. An outcome of "not yet resolved" is an acceptable final outcome for non-serious AEs at the end of a participant's participation in a study, and for SAEs at database lock.

The investigator should take appropriate diagnostic and therapeutic measures to minimise the risk to the participant. Where appropriate he/she should take diagnostic measures to collect evidence for clarification of the relationship between the SAE and the study drug.

The investigator must submit a complete “Serious Adverse Event Report” for all SAEs, regardless of a possible causal relationship. All reports of SAEs (initial and follow-up) must be reported to drug safety manager of the Sponsor (see Investigator’s Trial File and described in detail in the safety management plan for the trial) immediately (at the latest within 24 hours of having gained knowledge of the event).

The initial report should be as complete as possible; subsequent minor corrections or additions may be reported by re-submitting the amended initial SAE report. If relevant further information or information about the outcome becomes available, "Follow-up Reports" must be completed and sent to the Sponsor’s drug safety department. For all SAEs, the investigator is required to document in full the course of the SAE and any therapy given, including any relevant findings/records in the report.

All SAEs must also be recorded on the ‘Adverse Event Form’ of the eCRF.

Participants enrolled will be provided with a Clinical Trial Participant card at the time of IMP administration. This card will list contact details for the investigator.

